#### Recruitment Start Date

January 2020

#### Recruitment Due Date

November 2021

#### Study Due Date

June 2022

## Descriptive Elements of the Project

Large artery distensibility is physiologically important for cardiovascular efficiency. Distensible large arteries reduce impedance to systolic ejection and cardiac work, slows pulse wave velocity (PWV) so that the return of reflected pressure waves is delayed until after aortic valve closure, and favors coronary perfusion during diastole [1]. Conversely, stiffening of the central arteries results in an elevation in systolic blood pressure (SBP) and a lowering of diastolic blood pressure (DBP) which, in turn, increases left ventricular afterload and alters coronary artery perfusion [2]. These changes may result in left ventricular hypertrophy [3] and increased fatigue of arterial wall tissues [4], all of which substantially increase the risk of cardiovascular events and all-cause mortality [5, 6].

The sympathetic nervous system is a key regulator of blood pressure, and abnormal activity in this system is related to cardiovascular risk [7]. Specifically, indices of cardiac autonomic function such as heart rate recovery (HRR) and heart rate variability (HRV) are associated with brachial and aortic blood pressure [8, 9]. When measured after a maximal exercise effort, HRR and HRV are considered powerful independent predictors of mortality in healthy subjects and in various clinical populations [10-13].

In addition to their ability to predict cardiovascular event risk, arterial stiffness and indices of cardiac autonomic function are predictive of the success of different therapies [14, 15]. Cardiovascular medications including beta-blockers have been reported to reduce aortic PWV and wave reflection [14], most likely due to reductions in sympathetic activity [9, 16]. Additionally, a single bout of exercise has been shown to reduce both arterial stiffness (i.e., aortic PWV [17, 18]) and wave reflection (i.e., Alx and reflection magnitude; [19, 20]), and significantly impact on indices of cardiac autonomic function [18, 21-23].

This emerging area of research concerning “the physiology of recovery” may provide insights that could help optimize exercise recommendations for health and performance [24]. For example, not only some adaptations to physical training appear to result from the summation of acute effects of exercise bouts [25], as exercise-induced changes may be influenced by exercise mode with several studies reporting variable results [18, 26, 27]. HRR and HRV after maximal CPET vary according to whether exercise is performed on treadmill or cycle ergometer [28-30], since the physiological strain induced by treadmill exercise seems to be significantly greater than in cycle ergometer [31-33]. As for arterial stiffness, only a limited number of studies have directly compared exercise-induced acute changes in arterial stiffness (i.e., aortic PWV) following different exercise modes with discrete responses following each mode identified [18, 26].

Overall, these studies have focused on exercises rather on activities, to represent typical sessions in accordance with current guidelines for improvement and maintenance of cardiovascular health [34]. An obvious disadvantage rests on their reduced ecological validity [35, 36]. Participation in group fitness classes is increasingly common method by which individuals may fulfil the criteria set down in the ACSM guidelines for enhancing and maintaining cardiovascular fitness [34]. These can appropriately function to enhance measures of cardiorespiratory fitness when performed for at least 3 days/week for 30 minutes and induce favorable changes in cardiovascular risk profile [1-6]. The popularity of group fitness classes with the general public has been demonstrated for more than two decades and is most likely due to the social and non-competitive class environment. A broad range of group fitness classes are now available in both commercial and community fitness centers that incorporate a wide range of exercise modalities (e.g. stationary cycling, step classes, group resistance exercise, pilates and aerobic dance) using a combination of music and instructor choreographed routines and designed to accommodate varying fitness levels. However, despite the high participation rates of group fitness classes, no available data exists that describes and/or compares the vascular and autonomic responses and/or metabolic costs of different group fitness classes. In addition,

the extent to which participation in such classes may assist in the improvement of vascular and autonomic function, and whether there are periods of significant concern eventually caused by transient changes in arterial stiffness or autonomic function immediately following exercise.

## **Purpose**

The aim of this study was to compare the time-course of post-exercise parasympathetic reactivation of the heart and changes in local and regional indices of arterial stiffness to different fitness classes (Bike, Pump Power and Global Training), as prescribed for health [34] and commercially available.

## **Methodological Procedures**

### **Participants**

Twelve apparently healthy adults aged between 21 to 34 years will be included in this study. These will be recruited from the professional network of GCP. We do not expect these adults to be enrolled in any other scientific study besides PUMPING ARTERIES. Informed written consent will be signed by volunteers prior to the first evaluation day (Figure 1) in accordance with approval by the Ethical Committee of Faculdade de Motricidade Humana – Universidade de Lisboa. We expect recruited participants to be outwardly active with some experience in both aerobic and resistance exercise (~3–4 times/week, >3 months). No trained athletes will be included in the cohort. All participants will be healthy or perceived to be healthy based on the sport's medical examination or the preparticipation screening process. Exclusion criteria include any form of cardiovascular disease, more than one cardiovascular disease risk factor, resting hypertension (systolic blood pressure >140 mmHg, diastolic blood pressure > 90 mmHg), any prescription medication use, and currently smoking.

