### **Design**

The study is constructed as a randomized, cross-over, repeated-measures intervention. Participants will attend 4, separate, intervention sessions consisting of one group class of Bike, Pump Power, Global Training or no exercise (CON). There will be a minimum of 72 h between sessions [18, 37], and each session will consist of initial rest, experimental intervention, and recovery (Figure 1). Participants will be advised not to engage in any strenuous physical activity at least 48 hours before the study days. Body composition and cardiorespiratory fitness for each participant will be evaluated prior to- and following to- the CON session, respectively.

|                           | WEEK 1 |   |   |   |   |   |   | WEEK 2 |   |   |   |   |   |   | WEEK 3 |   |    |    |    |    |    |
|---------------------------|--------|---|---|---|---|---|---|--------|---|---|---|---|---|---|--------|---|----|----|----|----|----|
|                           | 1      | 2 | 3 | 4 | 5 | 6 | 7 | 1      | 2 | 3 | 4 | 5 | 6 | 7 | 8      | 9 | 10 | 11 | 12 | 13 | 14 |
| ENROLLMENT         |        |   |   |   |   |   |   |        |   |   |   |   |   |   |        |   |    |    |    |    |    |
| Eligibility Screen        |        |   |   |   |   |   |   |        |   |   |   |   |   |   |        |   |    |    |    |    |    |
| Randomization             |        |   |   |   |   |   |   |        |   |   |   |   |   |   |        |   |    |    |    |    |    |
| Informed Consent          |        |   |   |   |   |   |   |        |   |   |   |   |   |   |        |   |    |    |    |    |    |
| INTERVENTIONS*     |        |   |   |   |   |   |   |        |   |   |   |   |   |   |        |   |    |    |    |    |    |
| Bike                      |        |   |   |   |   |   |   |        |   |   |   |   |   |   |        |   |    |    |    |    |    |
| Pump Power                |        |   |   |   |   |   |   |        |   |   |   |   |   |   |        |   |    |    |    |    |    |
| Global Training           |        |   |   |   |   |   |   |        |   |   |   |   |   |   |        |   |    |    |    |    |    |
| Control                   |        |   |   |   |   |   |   |        |   |   |   |   |   |   |        |   |    |    |    |    |    |
| ASSESSMENTS        |        |   |   |   |   |   |   |        |   |   |   |   |   |   |        |   |    |    |    |    |    |

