**FIGURE 1: TIMELINE AND MAIN OUTCOME VARIABLES OF PUMPING ARTERIES**

\* INTERVENTIONS WILL BE RANDOMIZED. THE TIMELINE HEREIN DISPLAYED IS MERELY A GRAPHIC REPRESENTATION OF A PARTICIPANT'S ACTIVITIES FOLLOWING RANDOMIZATION.

In each session, participants will initially undertake 20-min of supine rest on a cushioned examination table with resting energy expenditure measured by indirect calorimetry (K5, Cosmed, Rome, Italy) and heart rate and blood pressure recorded continuously using digital plethysmography technique (Finapres® Nova, Ohmeda, 2 Louisville, Colorado, USA), followed by regional assessments of PWV and pulse wave analysis of the aortic, brachial and femoral arteries on the right side of the body using applanation tonometry (Colson Analyze, ALAM Medical, Paris, France), and carotid arterial stiffness indices and wave intensity analysis using an ultrasound (Arietta V60, Hitachi Aloka Medical Ltd, Mitaka-shi, Tokyo, Japan). In the time following, participants will perform one of three exercise sessions (Bike, Pump Power or Global Training). Exercise sessions will consist of either a 45-minute class of Bike, Pump Power, and Global Training, while energy expenditure will be continuously measured by indirect calorimetry (K5, Cosmed, Rome, Italy) (Figure 2). These sessions are characterized by distinct metabolic demands, representing the typical sessions provided by gyms and health clubs to improve or maintain cardiovascular health. In the control condition, the participants will remain quietly seated for 45-min, maintaining a good posture. Only one participant will be tested per class with approximately 10-20 non-research participants also performing each group fitness class alongside the research participants. Upon completion of each intervention/session, participants will return immediately to the examination table and recover in the supine position for 30-min while hemodynamic and stiffness indices are reevaluated at 10, 20- and 30-min following recovery and compared to those at rest.

|                       | Rest |    | Exercise Session | Recovery |    |    |
|-----------------------|------|----|------------------|----------|----|----|
|                       | 15   | 20 | 45               | 10       | 20 | 30 |
| Advanced Hemodynamics |      |    |                  |          |    |    |
| Arterial Stiffness    |      |    |                  |          |    |    |

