### **Statistical Analysis and Data Monitorization**

Based upon a medium effect size of 0.154 derived from published changes in aortic PWV within-between modes of exercise [18], an a priori power analysis suggested that 22 participants are required to detect significant differences within-between groups, conditions and time points ( $1-\beta = 80\%$ ,  $\alpha = 0.05$ ). All data will be collated and/or analyzed using Microsoft Excel (v15.29.1, Microsoft Corporation, Redmond, Washington, United States) and Statistical Package for the Social Sciences version 24 (IBM, Armonk, New York, United States) software with results presented as mean  $\pm$  SD. Due to technical issues, missing data (~4–5%) may be evident during the study and subsequently should be replaced by averaging values before and after the missing value for the relevant variable prior to analysis.

Comparisons between interventions (Bike, Pump Power, Global Training and Control) over time (Rest vs. post-intervention time points) for indices of autonomic and vascular function will be examined via two-way

(intervention × time), repeated measures analysis of variance (ANOVA) and adjusted for sex and activity energy expenditure. Session differences for indices of autonomic and vascular function and energy expenditure will be analyzed using a one-way repeated measures ANOVA. Post-hoc comparisons will be conducted via Bonferroni's tests. Statistical significance will be set at  $p < 0.05$ .

The database will be stored in the GCP private server throughout the study period. The GCP lab will be responsible for management, storage and is the single user of the complete database.

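### The protocol plans to include 12 participants, but its own power analysis requires 22; the two figures contradict each other and need reconciling

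*Protocol*

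**What the plan says.** Protocol, Participants: "Twelve apparently healthy adults aged between 21 to 34 years will be included in this study".

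Protocol, Statistical Analysis and Data Monitorization: "an a priori power analysis suggested that 22 participants are required to detect significant differences within-between groups, conditions and time points", with power 80% and alpha 0.05. The input is described thus: "Based upon a medium effect size of 0.154 derived from published changes in aortic PWV within-between modes of exercise [18"]. Neither the metric of that value nor the correlation between repeated measures is given.

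Protocol, Design: "The study is constructed as a randomized, cross-over, repeated-measures intervention", and "Participants will attend 4, separate, intervention sessions consisting of one group class of Bike, Pump Power, Global Training or no exercise (CON"). The text after Figure 1 adds that "hemodynamic and stiffness indices are reevaluated at 10, 20- and 30-min following recovery and compared to those at rest". That makes four time points: rest, 10, 20 and 30 minutes.

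The planned analysis is a two-way (intervention by time) repeated-measures ANOVA, covering "Comparisons between interventions (Bike, Pump Power, Global Training and Control) over time (Rest vs. post-intervention time points").

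**The concern.** Both numbers are current statements in the same document. One says how many people will be included and the other says how many are needed. A crossover has no arms to multiply by, so 12 cannot be a per-group figure that adds up to 22 or more. The protocol gives no other total, no reason for going below 22 and no revised power.

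The study's purpose is to compare the post-exercise time course between classes. If 12 are recruited while the 22-for-80% sentence stays in the protocol, a non-significant comparison may be judged against a power that the enrolment does not support. An ethics committee or a reader also cannot tell which number governs recruitment.

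**Working it through.** **Inputs from the protocol.** Planned enrolment 12 (Participants). Required N 22, power 0.80, alpha 0.05, effect size 0.154 (statistics section). Four interventions and four time points, all within participant (Design).

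**Inputs that must be assumed.** The metric of 0.154, the within-participant correlation ρ, and sphericity. The planned adjustment for sex and activity energy expenditure is left out.

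**Step 1. Can 22 be reproduced?** For the 4×4 within-participant interaction:

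- df1 = (4−1)(4−1) = 9
- df2 = 9(N−1)
- noncentrality λ = f²·N·16/(1−ρ)
- power = P(noncentral F > central F 0.95 quantile)

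With f = 0.154 and ρ = 0.5:

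- N = 22: λ = 0.023716 × 22 × 16 / 0.5 = 16.70, df2 = 189, power 81.0%
- N = 21: λ = 15.94, df2 = 180, power 78.6%

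The smallest N reaching 80% is therefore exactly 22. The protocol does not say that these settings were used, but they match its planned test and return its figure.

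**Step 2. The same settings at 12.** λ = 0.023716 × 12 × 16 / 0.5 = 9.11, df2 = 99, power 47.6%.

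**Step 3. A check that does not need the metric or ρ.** Choose λ so that N = 22 gives exactly 80%, multiply it by 12/22, and read off power at N = 12 with df2 = df1(N−1):

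| df1 | Power at 12 |
|---|---|
| 1 | 50.8% |
| 2 | 49.7% |
| 3 | 49.0% |
| 4 | 48.4% |
| 6 | 47.5% |
| 9 | 46.7% |
| 15 | 45.5% |

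So if 22 is right for 80%, power at 12 is about 46–51% for any of these fully within-participant tests.

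**Step 4. Detectable effect.** Under the Step 1 settings, the f detectable with exactly 80% power is 0.152 at N = 22 and 0.210 at N = 12, a ratio of 0.210/0.152 = 1.38. The simple scaling √(22/12) = 1.35 ignores the loss of denominator degrees of freedom and is slightly lower.

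**Step 5. Sensitivity to ρ** (4×4 interaction, 0.154 as f):

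| ρ | N needed for 80% | Power at 12 |
|---|---|---|
| 0 | 43 | 24% |
| 0.3 | 30 | 34% |
| 0.4 | 26 | 40% |
| 0.5 | 22 | 48% |
| 0.6 | 18 | 59% |
| 0.7 | 14 | 74% |
| 0.75 | 12 | 83% |
| 0.8 | 10 | 92% |

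The unstated correlation decides whether 12 is far too few or enough.

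**The case against.** The strongest reply is that the protocol attaches 80% to 22 participants and nowhere says that 12 gives 80%. A reader might infer that the trial claims a power it does not have. The text does not go that far: it does not show which number is operative, and if 22 was intended and the Participants section is the slip, there is no shortfall. This stands, so the point is a contradiction with a conditional consequence.

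A second reply is that 12 may be adequate. At ρ = 0.75 the table gives a required N of 12, and some other readings of 0.154 also return about 12. That is possible, but the protocol makes no such argument and says that 22 are required. The roughly 46–51% is therefore conditional on accepting the protocol's 22, and is not an absolute power.

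Two further criticisms are tempting and should not be made. A reader might infer that 22 cannot be reproduced because the inputs are incomplete, but Step 1 returns exactly 22 for the planned interaction under ordinary assumptions. A reader might also infer that 0.154 is mislabelled as medium. That depends on the metric: it does not fit the usual medium benchmarks for f (0.25) or partial eta-squared (0.06), but it is close to that for f-squared (0.15). The protocol gives no benchmark, and the source study is not at hand. What holds is only that the metric is unstated.

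The between-group part of the power statement could be defended as loose wording, since the ANOVA adjusts for sex. Sex is not an intervention group, though, and the crossover has no between-participant treatment factor.

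**Conclusion.** The contradiction is certain and needs no calculation: 12 planned against 22 required, a gap of 10, in a design where 12 can only be the total. It should be corrected before the protocol is relied on.

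The size of the consequence rests on accepting 22 as the number giving about 80% power. On that basis, enrolling 12 roughly halves the chance of missing nothing of the assumed size into a coin toss: power of about 46–51%, with a detectable effect about 1.4 times larger (from 0.154 to about 0.21 if the value is f). Without that acceptance, the stated inputs do not fix the power at 12. The documents do not show which of the two numbers is the mistaken one.

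**What to change.** State one sample size in both the Participants and the statistics sections.

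- **If 12 stands:** remove the statement that 22 are required for 80% power. Replace it with the power, or the detectable effect, at n = 12 for the within-participant intervention-by-time test on aortic PWV. Give the effect-size metric and the assumed within-participant correlation, and drop the between-groups wording. The cost is one recalculation and a few lines of text, with a less favourable figure likely unless a high correlation can be justified.
- **If 22 was intended:** correct the Participants section to 22. The wording change is trivial. Against a plan to recruit 12, it means 10 more participants and 10 × 4 = 40 more sessions, before any allowance for dropout. The metric, the correlation and the between-groups wording should be put right here too, so that the 22 can be checked.

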### **Design**

The study is constructed as a randomized, cross-over, repeated-measures intervention. Participants will attend 4, separate, intervention sessions consisting of one group class of Bike, Pump Power, Global Training or no exercise (CON). There will be a minimum of 72 h between sessions [18, 37], and each session will consist of initial rest, experimental intervention, and recovery (Figure 1). Participants will be advised not to engage in any strenuous physical activity at least 48 hours before the study days. Body composition and cardiorespiratory fitness for each participant will be evaluated prior to- and following to- the CON session, respectively.

|                           | WEEK 1 |   |   |   |   |   |   | WEEK 2 |   |   |   |   |   |   | WEEK 3 |   |    |    |    |    |    |
|---------------------------|--------|---|---|---|---|---|---|--------|---|---|---|---|---|---|--------|---|----|----|----|----|----|
|                           | 1      | 2 | 3 | 4 | 5 | 6 | 7 | 1      | 2 | 3 | 4 | 5 | 6 | 7 | 8      | 9 | 10 | 11 | 12 | 13 | 14 |
| ENROLLMENT         |        |   |   |   |   |   |   |        |   |   |   |   |   |   |        |   |    |    |    |    |    |
| Eligibility Screen        |        |   |   |   |   |   |   |        |   |   |   |   |   |   |        |   |    |    |    |    |    |
| Randomization             |        |   |   |   |   |   |   |        |   |   |   |   |   |   |        |   |    |    |    |    |    |
| Informed Consent          |        |   |   |   |   |   |   |        |   |   |   |   |   |   |        |   |    |    |    |    |    |
| INTERVENTIONS*     |        |   |   |   |   |   |   |        |   |   |   |   |   |   |        |   |    |    |    |    |    |
| Bike                      |        |   |   |   |   |   |   |        |   |   |   |   |   |   |        |   |    |    |    |    |    |
| Pump Power                |        |   |   |   |   |   |   |        |   |   |   |   |   |   |        |   |    |    |    |    |    |
| Global Training           |        |   |   |   |   |   |   |        |   |   |   |   |   |   |        |   |    |    |    |    |    |
| Control                   |        |   |   |   |   |   |   |        |   |   |   |   |   |   |        |   |    |    |    |    |    |
| ASSESSMENTS        |        |   |   |   |   |   |   |        |   |   |   |   |   |   |        |   |    |    |    |    |    |
| Body Composition          |        |   |   |   |   |   |   |        |   |   |   |   |   |   |        |   |    |    |    |    |    |
| Cardiorespiratory Fitness |        |   |   |   |   |   |   |        |   |   |   |   |   |   |        |   |    |    |    |    |    |
| Advanced Hemodynamics     |        |   |   |   |   |   |   |        |   |   |   |   |   |   |        |   |    |    |    |    |    |
| Arterial Stiffness        |        |   |   |   |   |   |   |        |   |   |   |   |   |   |        |   |    |    |    |    |    |
| Energy Expenditure        |        |   |   |   |   |   |   |        |   |   |   |   |   |   |        |   |    |    |    |    |    |

**FIGURE 1: TIMELINE AND MAIN OUTCOME VARIABLES OF PUMPING ARTERIES**

\* INTERVENTIONS WILL BE RANDOMIZED. THE TIMELINE HEREIN DISPLAYED IS MERELY A GRAPHIC REPRESENTATION OF A PARTICIPANT'S ACTIVITIES FOLLOWING RANDOMIZATION.

In each session, participants will initially undertake 20-min of supine rest on a cushioned examination table with resting energy expenditure measured by indirect calorimetry (K5, Cosmed, Rome, Italy) and heart rate and blood pressure recorded continuously using digital plethysmography technique (Finapres® Nova, Ohmeda, 2 Louisville, Colorado, USA), followed by regional assessments of PWV and pulse wave analysis of the aortic, brachial and femoral arteries on the right side of the body using applanation tonometry (Colson Analyze, ALAM Medical, Paris, France), and carotid arterial stiffness indices and wave intensity analysis using an ultrasound (Arietta V60, Hitachi Aloka Medical Ltd, Mitaka-shi, Tokyo, Japan). In the time following, participants will perform one of three exercise sessions (Bike, Pump Power or Global Training). Exercise sessions will consist of either a 45-minute class of Bike, Pump Power, and Global Training, while energy expenditure will be continuously measured by indirect calorimetry (K5, Cosmed, Rome, Italy) (Figure 2). These sessions are characterized by distinct metabolic demands, representing the typical sessions provided by gyms and health clubs to improve or maintain cardiovascular health. In the control condition, the participants will remain quietly seated for 45-min, maintaining a good posture. Only one participant will be tested per class with approximately 10-20 non-research participants also performing each group fitness class alongside the research participants. Upon completion of each intervention/session, participants will return immediately to the examination table and recover in the supine position for 30-min while hemodynamic and stiffness indices are reevaluated at 10, 20- and 30-min following recovery and compared to those at rest.

|                       | Rest |    | Exercise Session | Recovery |    |    |
|-----------------------|------|----|------------------|----------|----|----|
|                       | 15   | 20 | 45               | 10       | 20 | 30 |
| Advanced Hemodynamics |      |    |                  |          |    |    |
| Arterial Stiffness    |      |    |                  |          |    |    |
| Energy Expenditure    |      |    |                  |          |    |    |

